### Primary outcome

The primary outcome of this study is to estimate the difference in the mean QRISK3 score of patients receiving MULTI + compared to patients receiving TAU. QRISK3 is an algorithm that estimates the probability of developing cardiovascular disease over the next 10 years [43].

### Secondary outcomes

Below we describe the measurement instruments used in this study. The questionnaires, including a more detailed description and their psychometric properties can be found in the additional file on assessment instruments [see Additional file 1]. All questionnaires are administered in Dutch and all available Dutch versions of questionnaires are used.

#### Routine screening data

Routine screening data on somatic health, psychosocial functioning, substance use, medication use and PA is collected semi-annually in patients by trained HCPs.

Data on somatic health is used to calculate the QRISK3 score (i.e. HDL cholesterol, blood pressure, and BMI as calculated by dividing weight in kg by height in m^2^). Additionally, fasting glucose (mg/dL), triglycerides (mg/dL), weight (kg) and waist circumference are measured. Weight and waist circumference is measured to the first decimal (0.1 kg/cm) under the clothes at the level of the umbilicus (with the patient standing).

The Health of the Nations Outcomes Scale (HoNOS) is used to assess psychosocial functioning. The majority of patients will be measured with the HoNOS-12 [44]. The HoNOS 65 + [45] is used for ages 65 and above. The HoNOS-12 and HoNOS 65 + each have 12 items divided into four subscales.

Data on substance use is collected through routine questions about smoking (yes/no/stopped, if yes or stopped, how much on average; packyears are calculated), alcohol use (glasses per day, on average) and use of (soft)drugs (yes/no).

Medication related to cardiovascular health and diabetes, and psychotropic medication will be collected and converted into Defined Daily Dose (DDD) according the Anatomical Therapeutic Chemical Classification System from the World Health Organization (WHO) [46].

#### Lifestyle factors

##### *Physical Activity*

The Physical Activity Vital Sign (PaVs) is used to examine PA [47]. The PaVs is a 2-item questionnaire to assess whether patients meet the Dutch exercise guidelines for aerobic activity (yes/no). The PaVs for patients is obtained from routine screening. The PaVs is also assessed in HCPs through the online survey at each measurement.

The Simple Physical Activity Questionnaire (SIMPAQ) [48] is used to measure PA in addition to the PaVs. The SIMPAQ is a 5-item questionnaire which provides more detailed information about PA as compared to the PaVs and contains an additional measure on sedentary behaviour. The SIMPAQ is assessed in both patients and HCPs at each measurement.

##### *Diet and eating behaviour*

Diet will be assessed through a 24-h dietary recall (24HR) of all food and beverages consumed by patients. The Three Factor Eating Questionnaire-R18 (TFEQ-R18) is used to assess three domains of eating behaviour [49]. Diet and eating behaviour are assessed in patients at each measurement.

##### *Sleep and sleep medication*

The Scales for Outcomes in Parkinson’s disease sleep (SCOPA-Sleep) is used to evaluate sleep [50]. Additionally, information about the use of sleep medication is gathered. The SCOPA-Sleep is assessed in patients at each measurement.

#### Mental health outcomes

##### *Psychopathology*

The Brief Symptom Inventory (BSI) is used to measure symptoms of psychopathology [51]. The BSI consists of 53 items assessing nine symptom domains. The BSI is assessed in patients at each measurement.

##### *Quality of life*

Quality of life is measured with the EuroQol-5D (EQ-5D) [52] and the World Health Organisation Quality of Life-BREF (WHOQoL-BREF) [53]. The EQ-5D consists of five dimensions of health, with one item per dimension. The WHOQoL-BREF consists of four domains, measured through 24 items supplemented with two general health items. The EQ-5D is often used complementary to other quality of life instruments [54]. The EQ-5D and WHOQoL-BREF are assessed in patients at each measurement.

##### *Positive mental health*

The Mental Health Continuum – Short Form (MHC-SF) is used to examine positive mental health [55]. The MHC-SF measures positive mental health with 14 items, representing three domains of well-being. The MHC-SF is assessed in patients at each measurement.

#### Implementation factors

##### *Barriers and facilitators*

Barriers and facilitators regarding the implementation of MULTI + are assessed with the Measurement Instrument for Determinants of the Innovation (MIDI) [56]. This questionnaire consists of 29 items divided into four scales, which can be adapted to measure relevant constructs for the implementation. The MIDI can be used to identify which determinants influence the use of an innovation and improve or establish an implementation strategy. The MIDI is conducted in patients and HCPs, because both groups are considered end-users of MULTI + . The questions are adapted to fit the different end-users according to the manual. MIDIs are conducted in HCPs and patients before the implementation (Pre-MIDI) and after the implementation (Post-MIDI) of MULTI + . Thus, there are four different MIDIs available.

##### *Process evaluation*

To evaluate the implementation process and assess whether MULTI + is delivered as intended, a process evaluation will be conducted using the RE-AIM framework [57]. RE-AIM stands for the reach, effectiveness, adoption, implementation, and maintenance, and is often used to better interpret the effectiveness and implementation of an innovation. Data is continuously gathered from multiple sources, such as the facility services, patient files, questionnaires, and observations from research assistants.

##### *Adverse events*

Adverse events are investigated with an institutional program in which HCPs report and categorise incidents.

##### Motivation for behavioural regulation

Individual HCP factors, such as self-determined motivation, may influence the promotion of a healthy lifestyle in patients [58]. To assess motivation for behavioural regulation in exercise, the Behavioural Regulation in Exercise Questionnaire (BREQ-2) is used [59]. The BREQ-2 is comprised of 19 items divided into five scales. Furthermore, the BREQ-2 is used to devise a questionnaire assessing the motivation for Behavioural Regulation in Diet Questionnaire (BRDQ). All items used in the BREQ-2 assessing behavioural regulation in exercise were converted by changing the word “exercise” to “(eat a) healthy diet”. Both versions of the BREQ-2 are assessed in HCPs at each measurement.

##### Health Technology Assessment (HTA)

Cost-effectiveness is investigated through calculation of the costs of TAU as compared to costs of MULTI + . This social cost benefit analysis uses data from patient files to determine the costs of care used in the different conditions (TAU vs. MULTI +), and medication costs based on DDDs. Additionally, for the subgroup that answered questions regarding quality of life, we investigate impact on quality of life as opposed to costs. The total costs per measuring moment per patient is used as an outcome measure and expressed in euros.

### Research procedures

#### Recruitment

The implementation team informs the HCPs about the measurement procedures. Patients are informed about the study through HCPs and members of the implementation team (see Table 3 for participant timeline). Promotion materials will be used (such as videos, flyers and posters) to give information about the study.

**Table 3 Tab3:** *Participant timeline*

Parameters		Time of Measurement			
		T0 (baseline)	T1 (six months)	T2 (twelve months)	T3 (eighteen months)
Informed consent^a^	PT & HCPs	x			
Demographics^a^	PT & HCPs	x			
Routine screening data^b^	EPR	x	x	x	x
Semi-structured interviews	PT	x	x	x	x
Online surveys	HCPs	x	x	x	x
Process evaluation	ongoing evaluation				
Adverse events					
Costs					

*PT* Patient, *HCPs* Health Care Professionals, *EPR* Electronic Patient Record

^a^Or at first enrolment in the study

^b^Data from routine screening is extracted from the EPR

#### Informed consent

Informed consent of HCPs is obtained online. With permission from the Medical Ethical Commission (METC), patients give verbal informed consent using a visual informed consent (VIC). A VIC is a visualisation of the goal and procedures of the study, and usage of personal data. The VIC makes information about the study easier to comprehend for patients. Researchers and research assistants are trained to conduct the informed consent procedure verbally. Patients will not be included in the study if they do not understand the information given, as deemed by HCPs or researchers.

#### Procedural considerations

The semi-structured interviews are conducted in a suitable place as determined by the researchers, HCPs and patients. If a patient is unable to adequately answer all questions, HCPs are asked for support when possible. If participating patients decease or discontinue inpatient treatment, they will not be included for further data collection. Data collected up until that point will be used for analyses. When patients withdraw consent, data already collected will be stored according to data protocol and Dutch law but will not be used for analyses or publications. After each measurement, 50 gift vouchers of 10 euros will be raffled among patients. HCPs will receive a small gift at ward level (such as a fruit basket or a water jug).

#### Study status

At the time of this manuscript submission data collection has commenced and final measurement is expected in August 2022.

### Statistical analyses

Within each cluster-intervention period (cluster I and TAU, cluster I and MULTI + , cluster II and TAU, cluster II and MULTI + etc.) we will analyse the QRISK3 of patients treated in that period. We select the last known measurements for each patient (longest exposure). For each of these measurements, the duration of exposure of patients in this cluster is calculated (date of last measurement minus day of entering this period). A proportion of patients will experience the switch in intervention during their stay. In such individuals, we will analyse both measurements reflecting the different conditions. The correlation of between subject measurements will be taken into account by adding a random effect for subjects. All QRISK3 data points will be analysed with mixed model analyses. We will analyse the logit transformed QRISK3 probabilities for similar reasons as in logistic regression, namely to avoid problems of estimating probabilities below 0 or above one and because it is more likely that the effect of treatment and other covariates on the outcome will be constant on the relative odds ratio scale.

The linear mixed model will contain: treatment (binary, 1/0 coding), cluster (categorical, two levels, dummy variables), time period (categorical, four levels, dummy variables), random effect for subject, the duration of exposure (continuous, restricted cubic splines with three knots); and the following potential confounding variables: age (continuous), key diagnostic subgroups (categorical) and illness severity (continuous).

Multiple imputation will be used to account for missing values. The same variables will be used in the imputation model as in the analysis model, extended with characteristics related to these variables. Multiple imputation based on chained equations will be used to generate 10 imputation sets (or more if the number of missing values is larger than expected). Results from imputed datasets will be pooled using Rubin’s rules.

Although MULTI + will be integrated into routine clinical care regardless of specific inpatient facility setting, we pragmatically set a minimum of 10 days exposure, assuming that we cannot expect an effect within a few days of hospitalization.

Explorative subgroup analyses will be performed to gain insight in possible treatment differences between the subgroups gender (categorical) age (continuous) and subjects with repeated-measures. Subgroup analyses will be performed consecutively by adding the main effect of these variables and their interaction to the main model specified above.

All analyses will be conducted with IBM SPSS statistics 25 and R version 4.0.4 or higher, with a 95% confidence interval (*p* < 0.05) and will be corrected for multiple outcomes/comparisons (Bonferroni correction) if necessary.

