## Discussion

This study protocol has been designed to evaluate the effectiveness and implementation of MULTI + in a specialist mental healthcare organisation with ~ 830 places of residence. To our knowledge, this will be the first large-scale study evaluating the long-term effects of a multidisciplinary, multicomponent approach aimed at improving lifestyle factors in routine inpatient clinical care. This study builds on previous research, which showed improvements on both physical and mental health outcomes in patients, and the need for more organisational support to continue and expand its implementation [32].

A reduction of ≥ 5% loss of body weight is associated with a relevant reduction in cardiovascular risk [60], which we therefore originally considered as the primary outcome of this study [61]. However, this was reconsidered after observing the high-patient turnover hindering individual follow-up and several other substantive considerations. Predominantly, this outcome measure does not account for other known risk factors for developing CVD, such as familial history, age, smoking behaviour, total cholesterol level, presence of mental illness and the use of atypical antipsychotics. By not taking these risk factors into account, the risk of CVD is often underestimated in people with MI and outcomes can be misinterpreted (e.g., lack of weight loss while reducing smoking behaviour) [62]. QRISK3 is a risk calculator that estimates individual risk of developing CVD in people between 25–84 years old, using multiple predictor variables that are especially relevant for people with MI. Therefore, the primary aim of this study is to investigate the difference in the mean QRISK3 score of patients receiving MULTI + compared to patients receiving TAU. To our knowledge there are no risk calculators suitable for ages under 25. Inpatients < 25 will therefore be excluded from this analysis, but will be included for secondary outcomes.

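### The primary outcome is a difference in mean QRISK3, but the specified model estimates a difference in mean logit QRISK3, and the text does not link the two

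*Protocol article*

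**What the plan says.** The Primary outcome section sets the target: "to estimate the difference in the mean QRISK3 score of patients receiving MULTI + compared to patients receiving TAU". The Abstract states the same contrast, and the Discussion repeats it: "the primary aim of this study is to investigate the difference in the mean QRISK3 score". The scale is that of a probability: "QRISK3 is an algorithm that estimates the probability of developing cardiovascular disease over the next 10 years".

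The Statistical analyses section puts the response on another scale: "We will analyse the logit transformed QRISK3 probabilities for similar reasons as in logistic regression". Treatment enters once, as a single 0/1 term: "The linear mixed model will contain: treatment (binary, 1/0 coding". Two reasons are given for the logit. It keeps estimated probabilities between 0 and 1, and "it is more likely that the effect of treatment and other covariates on the outcome will be constant on the relative odds ratio scale".

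No section restates the primary outcome on the logit or odds scale. None says how the treatment coefficient is to be turned into a difference in mean QRISK3.

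**The concern.** The logit of an average is not the average of the logits. A linear model for logit(QRISK3) estimates a shift in the average logit, whereas the stated outcome is a shift in the average probability. The two weight patients differently. On the logit scale a fall from 1% to 0.8% counts about as much as a fall from 20% to 17%, but the second contributes fifteen times as much to the mean risk (3 points against 0.2).

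At stake is the headline estimate. Read as written, the analysis yields an odds-scale contrast. A reader who wants the promised difference in mean QRISK3 cannot recover it from the coefficient alone, and the obvious shortcut of back-transforming at the average logit gives a number that is too small.

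**Working it through.** **Inputs.** The target (difference in mean QRISK3), the response (logit QRISK3) and the single treatment term come from the sections cited above. The documents give no QRISK3 distribution, and the Sample size section says that no relevant data on QRISK3 changes were available for this population. The medians, logit standard deviations (SD) and odds ratios (OR) below are therefore assumptions. The plan gives no figure on this point to reproduce, because its sample size rests on body weight.

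**Step 1: the two quantities.** Let p be QRISK3 and L = ln(p/(1-p)).
- Stated outcome: D = E[p | MULTI+] - E[p | TAU].
- Model coefficient: b = E[L | MULTI+] - E[L | TAU], adjusted for covariates. Then exp(b) is a ratio of geometric-mean odds.

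**Step 2: weighting.**
- 1% to 0.8%: logit(0.008) - logit(0.01) = -0.225.
- 20% to 17%: logit(0.17) - logit(0.20) = -0.199.

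**Step 3: constant odds ratio, unchanged spread.** Take L normal with mean logit(median) and the stated SD under TAU, and shift it by ln(0.90) = -0.105 under MULTI+. Integrating expit(L) over each distribution gives D. The simple back-transform is expit(logit(median) + ln 0.90) - median.

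| Median QRISK3 | SD of logit | Mean, TAU | Mean, MULTI+ | D (points) | Simple back-transform (points) |
|---|---|---|---|---|---|
| 3% | 1.0 | 4.55% | 4.14% | -0.41 | -0.29 |
| 6% | 1.2 | 9.67% | 8.89% | -0.78 | -0.57 |
| 10% | 1.2 | 14.69% | 13.61% | -1.08 | -0.91 |
| 15% | 1.0 | 18.85% | 17.48% | -1.37 | -1.29 |

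One coefficient maps to about a threefold range of D (1.37/0.41 = 3.3). The simple back-transform recovers between 70% and 95% of it. The gap widens with a larger spread and a larger effect: at OR 0.80, median 3% and SD 1.5, D is -1.10 points (6.72% to 5.63%) and the simple back-transform gives -0.59.

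Every row has the same sign. A common shift of L moves every p in the same direction, so b = 0 exactly when D = 0.

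**Step 4: what a difference in sign would need.**
- *Effect varying with baseline risk.* Half the patients are at 2% with OR 0.8, and half at 20% with OR 1.1. Then b = (ln 0.8 + ln 1.1)/2 = (-0.223 + 0.095)/2 = -0.064, so OR 0.94. The risks become 1.61% and 21.57%, so D = (-0.39 + 1.57)/2 = +0.59 points.
- *Spread changing between conditions.* With median 5%, SD 1.0 under TAU and OR 0.90, D is zero if the SD under MULTI+ is 1.135, and positive above that.

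**The case against.** The strongest reply is that this is a reporting detail. Fitting on a transformed scale and presenting results on the natural scale is ordinary practice. The first reason given for the logit, avoiding impossible probabilities, suggests that risks on the natural scale are in view. An analysis plan that is not shown may contain the step. This carries weight: nothing in the article rules out back-transformed reporting, and the logit itself is a reasoned choice. What remains is that the article specifies the primary analysis down to spline knots and number of imputations, names one quantity as the outcome, models another, and does not connect them. The back-transform that a reader would try first is also not the right one.

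A reader might go further and infer that the planned analysis tests the wrong hypothesis, or is liable to show benefit where mean risk rises. The documents do not support that. Under the constant odds ratio that the article considers more likely, with unchanged spread, the null hypothesis and the direction are the same on both scales. The two-group example in the working needs benefit at low risk and harm at high risk, and nothing in the article suggests that MULTI+ raises risk in high-risk patients. The heterogeneity of patients, the tailoring by ward and the exploratory interactions with age and gender make a varying effect plausible, but they do not imply opposite effects.

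It is also fair to say that one sentence naming the odds-scale contrast as the primary estimate would remove the inconsistency. That would change the stated outcome, however, and not deliver it.

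**Conclusion.** The mismatch stands: the stated primary outcome and the model's treatment term are different quantities, and the article does not link them. Its consequence is for the size and interpretation of the primary estimate, and not for the validity of the logit model or, under the article's own working assumption, of its test. The range of -0.4 to -1.4 points for OR 0.90 and the size of the back-transformation error depend on the assumed logit-normal distributions and would change with the real data. A difference in sign is only a conditional possibility. It is worth correcting because it concerns the headline result and is cheap to put right.

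**What to change.** Keep the logit mixed model and its test of treatment. State that the primary effect estimate is the standardised difference in mean QRISK3, obtained as follows:

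1. From the fitted model, predict every analysed record under MULTI+ and again under TAU.
2. Back-transform each prediction to a probability with the between-subject and residual variation included, and not at the mean logit alone.
3. Average over records under each condition and take the difference.
4. Give a confidence interval by bootstrap or delta method, and pool over the imputed datasets.
5. Report the odds ratio from the treatment coefficient alongside.

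The cost is a little more analysis code and no new data. The back-transform relies on the model's distributional assumption for the random effect and residuals, so that assumption should be checked.

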**Methods:**

An open cohort stepped wedge cluster randomized trial in inpatients psychiatric wards of GGz Centraal, the Netherlands. The wards are divided into three clusters based on geographical region. These clusters are randomly allocated to one of the three pre-defined steps to integrate MULTI + . MULTI + can be tailored to fit individual psychiatric wards and includes 10 core components aimed at improving lifestyle factors. The primary outcome is to investigate the difference in the mean QRISK3 score of patients receiving MULTI + compared to patients receiving TAU. Secondary outcomes include somatic and mental health outcomes, lifestyle factors, and implementation factors. Findings will be analysed using mixed model analyses.

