## Methods

### Study design and setting

This study is an open cohort stepped wedge cluster randomized trial conducted at all inpatient wards of the specialist mental healthcare organisation GGz Centraal (the Netherlands) [34]. The organisation will implement MULTI + semi-annually in three geographical regions (clusters). Wards are almost equally distributed per cluster, covering a total of ~ 830 places of residence in which ~ 2000 patients are treated annually (Table 1). This gradual implementation intends that all clusters are exposed to MULTI + at the end of this trial. Each step includes a one-month transitional phase to prepare the cluster for the implementation of MULTI + . This trial takes 18 months to complete.

**Table 1 Tab1:** *Places of residence divided in three clusters*

**Cluster**	**Wards (n)**	**Places of residence (n)**
1	15	~ 300
2	14	~ 300
3	15	~ 230

In line with the regional implementation, cluster-level randomisation is used. Individual-level randomisation is not possible because patients cohabit in groups within wards. Moreover, cluster-level randomisation minimizes the risk for contamination between HCPs working in multiple wards or different geographical clusters. Due to high patient turnover the patient population may differ at each measurement and individual follow-up for long-term evaluation is not feasible after discharge.

Measurements are obtained at the same time in all clusters at baseline (T0), after six months (T1), after twelve months (T2) and after eighteen months (T3). Measurements take approximately three months to complete (Fig. 1).

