### Intervention

MULTI + is a multidisciplinary, multicomponent intervention which aims to improve lifestyle factors through a holistic approach. MULTI + focuses on 10 core components (i.e. the elements and activities that are necessary to achieve desired outcomes) [35], based on previous research and recommendations (Table 2) [5, 14, 30]. MULTI + is embedded in the long-term policy of the mental health care organisation, creating a support base and resources to facilitate implementation at all organisational levels. The implementation of the core components is co-designed with, and tailored to the ward and patient population, because of the large heterogeneity in patient characteristics and varying access to facilities and staffing.

**Table 2 Tab2:** *10 core components of MULTI + and application into routine clinical care*

Core components of MULTI + ^a^	Application of core components
Routine daily structure and sleep	Wards offer a routine structure in a day-to-day program which includes standard mealtimes, sports-related activities, work-related activities, psychoeducation, and skills training. HCPs pay attention to the circadian rhythm and sleep hygiene of patients. It is intended that patients participate in at least two activities per day, such as walking in the morning and psychoeducation in the afternoon. HCPs motivate patients to engage in activities
Physical activity	Decreasing sedentary behaviour and increasing PA with the credo: “doing some physical activity is better than doing none” as a starting point. The eventual aim is to meet the (inter)national physical activity guidelines of ≥ 150 min of moderate-intensity PA every week, spread over several days [36, 37]. Additionally, patients engage in muscle- and bone-strengthening activities at least twice a week. Elderly patients combine these with balance exercises
Attention to nutrition and eating habits	Attention for the nutritional value and composition of meals and snacks in compliance with the Dutch national guidelines [38], as well as eating habits such as mealtimes and mindful eating. There are (preventive) consultations with dietitians on (clinical) indication of patients or HCPs
Substance use	Smoking cessation is encouraged in both HCPs and patients, and patients are supported by smoking interventions on (clinical) indication of patients or HPCs. For other substance use, patients are referred to addiction specialists

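### The primary model has no cluster-by-period or ward-by-period term, so its standard errors are too small if regions or wards drift differently over time; it also gives the three clusters two levels

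*Protocol article*

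**What the plan says.** The abstract states the unit of allocation: "The wards are divided into three clusters based on geographical region". Table 1 gives 15, 14 and 15 wards, 44 in all. Under Study design and setting, the reason for cluster allocation is that "Individual-level randomisation is not possible because patients cohabit in groups within wards". Under Intervention, delivery is "co-designed with, and tailored to the ward and patient population".

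The Statistical analyses section then fixes the primary model for logit QRISK3: binary treatment, an exposure-duration spline, age, diagnostic subgroup, illness severity, and "cluster (categorical, two levels, dummy variables), time period (categorical, four levels, dummy variables), random effect for subject". The only correlation it mentions is that of repeated measurements, which "will be taken into account by adding a random effect for subjects". It lists no term for ward, ward-by-period or cluster-by-period.

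The Sample size section uses a single correlation of 0.1, says that knowledge on this is insufficient, and arrives at 846 patients for 80% power on a loss of at least 5% of body weight. The Discussion concedes that outside events and changes in the organisation may affect results and be hard to adjust for.

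**The concern.** In a stepped wedge, treatment is estimated from how regions differ from one another within periods after allowing for their stable differences. A shift in one region in one period (staffing, an outbreak, a change in who is admitted) looks the same as a treatment effect. With three regions, few such shifts average out, and more patients per region do not help. A model that treats patients as independent, apart from their own repeated measurements, puts no such variation into the standard error. The confidence interval is then too narrow and a chance regional shift can be declared an effect of MULTI+. Because the article writes the model out term by term, this is a stated choice and not a detail left to a fuller plan.

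The cluster coding is a separate inconsistency in the same sentence. Four levels for period counts the four occasions T0 to T3. Read the same way, two levels for cluster is one short.

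**Working it through.** **Inputs from the protocol article.** 3 regions; 44 wards; 4 occasions; 16.3% versus 32%; 5% significance; 80% power; 10% dropout; correlation 0.1; 846 patients; turnover of about 2000. **Assumed:** two-sided test; equal cell sizes; the region-by-period share *r* of total variance, which the document does not give.

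**1. Reproducing 846.** With mean proportion 0.2415 and difference 0.157, the two-proportion formula gives 115.5, so 116 per arm (232). The stepped-wedge variance for three regions, three steps and one baseline period, with correlation 0.1 *constant over time*, needs 62 per region-period. That is 12 × 62 = 744, and 744/0.9 = 827, which is 2.2% below 846. The figure is therefore reproduced closely with no region-by-period variance.

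**2. Information at the level of randomisation.** There are 3 × 4 = 12 region-period cells. Fixed parameters: 1 intercept + 2 region + 3 period + 1 treatment = 7. Residual degrees of freedom: 12 − 7 = 5. The weights of the treatment estimate on the 12 cell means are:

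| Region (in step order) | T0 | T1 | T2 | T3 |
|---|---|---|---|---|
| First | −0.3 | 0.5 | 0.1 | −0.3 |
| Second | 0 | −0.4 | 0.4 | 0 |
| Third | 0.3 | −0.1 | −0.5 | 0.3 |

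Each row and each column sums to zero, so stable regional differences and shifts common to all regions cancel. A shift confined to one cell does not: one unit in the first region at T1 moves the estimate by 0.5.

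**3. Type I error.** With *m* records per cell, the ratio of true to assumed variance is (1 − r) + m·r, and type I error is 2[1 − Φ(1.96/√ratio)]. After dropout 846 × 0.9 ≈ 762, so m = 762/12 = 63.5. For 2000, m = 166.7.

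| r (assumed) | Ratio, 762 | Type I | Ratio, 2000 | Type I |
|---|---|---|---|---|
| 0 | 1.00 | 5.0% | 1.00 | 5.0% |
| 0.005 | 1.31 | 8.7% | 1.83 | 14.7% |
| 0.01 | 1.625 | 12.4% | 2.66 | 22.9% |
| 0.02 | 2.25 | 19.1% | 4.31 | 34.5% |

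A simulation with the subject random effect, 44 wards, a stable ward share of 0.05 and an assumed 30% of patients measured under both conditions (within-subject correlation 0.8, assumed) gave higher values for r = 0.005, 0.01 and 0.02: 13.2%, 23.3% and 27.7% at 846 patients (600 runs), and 25.3%, 36.0% and 47.7% at 2000 (300 runs). An analysis of the 12 cell means with 5 degrees of freedom held 4.9 to 5.2% in every scenario tested.

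**4. Wards.** Stable ward shares of 0.05 to 0.10 give 4.4 to 3.9% by formula; simulation at a share of 0.05 gives 4.7% (846) and 6.0% (2000, within simulation error). There is no inflation. Ward-by-period shares of 0.02 to 0.05 give 5.9 to 7.2% by formula at 846 (simulated 7.5 to 8.5%) and 7.4 to 11.2% at 2000 (simulated 9.0 to 20.7%).

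**5. Power for the weight-loss endpoint.** Variance per patient is 0.2415 × 0.7585 = 0.1832, and the squared weights in step 2 sum to 1.2. With region as a fixed effect, SE² = 0.1832 × 1.2 × (r + 0.9/62). The range in each cell runs from region fixed to region random (the latter as in step 1), at 744 analysed.

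| r, out of the 0.1 | SE | Power, normal test | Power, 5 df |
|---|---|---|---|
| 0 | 0.0565–0.0559 | 79–80% | 61–62% |
| 0.005 | 0.0655–0.0646 | 67–68% | 49–50% |
| 0.01 | 0.0734–0.0720 | 57–59% | 41–42% |

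**The case against.** **The inflation is not established.** A reader might infer from the missing terms that the false-positive rate is well above 5%. The protocol does not support that: it gives no region-by-period or ward-by-period variance, and with a zero share the error is 5.0%. This objection stands, and the figures above are conditional.

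**Omitting wards is not in itself the fault.** A reader might also infer that leaving out 44 wards must shrink the standard errors. Stable ward differences cancel within region, so only ward changes over time matter, and their effect at 846 patients is modest. This stands too. A ward intercept alone would repair nothing.

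**Two levels is probably a slip.** Taken literally, it would pool two regions. Then 52% (first with second, or second with third) or 75% (first with third) of their true difference would enter the treatment coefficient. But the same section numbers the clusters and mentions dummy variables, and the rest of the article has three clusters, so two dummy variables is the natural reading. Nothing shows that pooling is planned. The wording still needs correcting.

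**The calculation simplifies.** The plan takes each patient's last measurement under each condition, so cells will be unequal. The age, diagnosis and severity covariates would absorb part of any change in case mix. Organisation-wide events are absorbed by the period effects. The exact percentages are therefore not this trial's own. These points may reduce the region-by-period share, but they do not put what remains into the standard error.

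**Degrees of freedom and endpoint.** The article does not state how degrees of freedom are obtained, and that can be left to a fuller plan. The power figures concern weight loss, not QRISK3. Both points are fair. The missing random terms remain a feature of the model as written.

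**Conclusion.** The concern holds in conditional form. The model as listed makes no allowance for regions or wards moving differently over time, and with three randomised regions its standard errors are too small whenever they do. A region-by-period share of 0.01, one tenth of the correlation that the sponsor itself assumes, takes type I error to about 12% at 762 records and 23% at 2000. At 0.02 it is about 19% and 35%, and at zero it is 5%. The problem grows with the number of patients, so the large turnover is no protection. These values rest on assumed shares, equal cells, no covariates and a normal test. Tailoring by ward and the article's own caution about outside events make a non-zero share plausible, but do not measure it. The two-level coding contradicts the three clusters stated elsewhere; it is a wording error with no demonstrated effect on the results.

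**What to change.** In Statistical analyses:

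- Describe cluster as categorical with three levels, entered as two dummy variables.
- Add random intercepts for ward, ward-by-period and cluster-by-period, with a small-sample degrees-of-freedom correction such as Kenward-Roger.
- Report the analysis of the 12 region-period means (5 df) as a supporting sensitivity analysis. It should not be a gatekeeper for any claim, since its power is only about 41 to 50% at the shares considered. It is useful because a cluster-by-period variance resting on 5 degrees of freedom will be imprecise.

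In Sample size, state that 80% power at 846 is for the weight-loss endpoint and assumes the 0.1 correlation is constant over time. State also that power falls to about 67–68% or 57–59% (normal test; lower with 5 df) if 0.005 or 0.01 of the variance is region-by-period.

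No new data are needed provided ward is held in the patient file, and the change can be dated before the analysis. The price is wider intervals (critical value 2.57 with 5 df against 1.96) and a less favourable stated power.
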